**Fig. 1 Fig1:**
[figure not shown]
Study flow chart

### Study setting

Researchers in the Faculty of Health, Science and Technology, Oxford Brookes University, will coordinate the study. The intervention is designed as a website and will be self-managed by participants at home, with HCP support taking place via phone/video calls. Usual care will involve ICU follow-up services to patients at the three sites.

### Participants

#### Inclusion criteria

Patient participants will be eligible for inclusion if they (i) are adults ≥ 18 years; (ii) have been in an ICU for a minimum of 72 h; (iii) have required Level 3 care (failure of two or more organs and/or requiring advanced respiratory care) [21] during their ICU stay; (iv) self-report symptoms of fatigue at the point of discharge (± 7 days) from hospital (≤ 34/52) on the validated Functional Assessment of Chronic Illness Therapy-Fatigue (FACIT-F) additional concerns subscale [37]; (v) are ready for discharge from hospital (± 7 days); and (vi) are willing and able to comply with the study protocol requirements and procedures.

#### Exclusion criteria

Prospective patient participants will be excluded if they (i) are expected to survive for ≤ 30 days according to their clinical team and (ii) have a neurological diagnosis occurring as a cause or result of the patient ICU admission (e.g. stroke, traumatic brain injury) or any neurodegenerative condition (e.g. multiple sclerosis, amyotrophic lateral sclerosis) as these specialist groups have different clinical and biological characteristics.

### Sample size

Based on our case-mix data, we have a target sample of 70 participants with 1:1 randomised to the intervention and control arms. As this is a feasibility trial, a power calculation has not been conducted. Seventy participants would provide adequate feasibility data [35] and allow timely completion of the study. Anticipating a participant retention rate of 80%, we estimated that a target sample of 70 would allow us to calculate retention with a margin of error of approximately 18% with a 95% confidence level. This sample size was deemed sufficient to inform the future RCT and to provide adequate analysis of the study’s progression criteria.

HCPs involved in the delivery of the intervention at each site will be purposely sampled from each site. It is anticipated that 2–5 HCPs from each site will be involved in the intervention delivery. Eligible HCPs will include those registered with a professional body (Nursing and Midwifery Council, General Medical Council, Health, and Care Professionals Council) and who are directly involved in the delivery of the intervention for this study.

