#### Primary outcome measures

The primary outcome focuses on the willingness of people affected by fatigue after critical illness to participate in an RCT evaluating an HCP-supported, self-management intervention. Recruitment and retention rates are critical indicators.

Recruitment rate is defined as the number of participants recruited or randomised as a proportion of those eligible and approached. This rate will be assessed at baseline and calculated both overall and by the research site.

Retention rate is defined as the proportion of participants who complete all the required questionnaires and semi-structured interviews. This outcome is essential to evaluate participant engagement and the feasibility of collecting follow-up data.

Assessments will be completed via phone or video call at baseline, three months, and six months post-randomisation. During the baseline data collection phase, additional demographic information (including age, sex, ethnicity, employment status, and marital status) and medical history (including comorbidities, primary diagnosis on ICU admission, ICU length of stay, hospital length of stay, days of mechanical ventilation, and severity of illness assessed by the APACHE III [22] will also be collected.

The progression criteria for full trial are summarised in Table 1.

**Table 1 Tab1:** Progression criteria

Category	Recruitment	Retention and follow-up completion	Remedial action
Green (Go)	> 85% anticipated (> 60 participants)	At least 80% of survivors will provide complete follow-up data	Continue—no action needed. Apply for further funding
Amber (Amend)	50–85% anticipated (36–75 participants)	60–80% of survivors will provide complete follow-up data	Continue—action needed. Explore ways to improve recruitment/retention
Red (Stop)	< 50% anticipated (< 35 participants)	< 60% of survivors will complete follow-up data	Stop. Explore reasons for poor recruitment/retention

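### The 18% margin of error quoted for retention with 70 participants is about 1.9 times what its own inputs give (9.4 percentage points)

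*Protocol article*

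**What the plan says.** The Sample size section gives a target of 70, allocated 1:1, and explains that "As this is a feasibility trial, a power calculation has not been conducted". In place of power it offers one precision statement. It takes 80% as the anticipated retention and concludes that "a target sample of 70 would allow us to calculate retention with a margin of error of approximately 18% with a 95% confidence level". The next sentence calls the size sufficient for planning the later trial and for analysing the progression criteria.

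Under Primary outcome measures, retention is a single proportion: "Retention rate is defined as the proportion of participants who complete all the required questionnaires and semi-structured interviews". Table 1 judges it on percentage bands. Green is "At least 80% of survivors will provide complete follow-up data", Amber is 60–80% and Red is below 60%.

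No formula accompanies the 18%. Nothing says that it is a full interval width, a per-arm figure or a between-arm figure, and no other numerical precision figure appears in the article.

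**The concern.** A margin of error is conventionally the ± half-width of a confidence interval. The sentence supplies everything needed to calculate it: one proportion (80%), one sample size (70) and one confidence level (95%). Those inputs give roughly half the stated figure.

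Retention is named within the primary outcome and is one of the two progression criteria. A reader who takes the sentence literally would expect an interval of 62% to 98% around 80% retention, which covers nearly all of the Amber band. The inputs support a much tighter interval. A funder, or a statistician planning the definitive trial, would misjudge how well this study can estimate retention and might carry the same factor of about two into later planning.

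**Working it through.** **Inputs, all from the Sample size section**
- Retention p = 0.80.
- Sample size n = 70, or 35 per arm under 1:1 allocation.
- Confidence 95%, so z = 1.96.
- Stated result: "margin of error of approximately 18% with a 95% confidence level".

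**Step 1. Try to reproduce the stated figure as worded.** For one proportion, the margin is z × √(p(1 − p)/n):

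1.96 × √(0.80 × 0.20/70) = 1.96 × √(0.16/70) = 0.0937, or 9.4 points.

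The interval is 80 ± 9.4, that is 70.6% to 89.4%. The ratio of stated to calculated margin is 18/9.37 = 1.92. The 18% is not reproduced.

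**Step 2. Try other half-widths for a single proportion.**

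| Variant | Half-width (points) |
|---|---|
| Wilson, 56/70 (69.2% to 87.7%) | 9.3 |
| Exact (Clopper-Pearson), 56/70 (68.7% to 88.6%) | 9.9 |
| Wald with continuity correction, n = 70 | 10.1 |
| Worst case p = 0.5, n = 70 | 11.7 |
| 99% confidence, n = 70 | 12.3 |
| n = 56 (80% of 70), p = 0.80 | 10.5 |
| One arm, n = 35, p = 0.80 | 13.3 |
| One arm after 20% loss, n = 28, p = 0.80 | 14.8 |

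None reaches 18. A few unusual combinations come near it: one arm of 35 at 99% confidence (17.4), one arm of 28 at p = 0.5 (18.5), and the lower limb of a Jeffreys interval for one arm of 28 (18.9). Each departs from the stated sample size, and the first two also depart from the stated confidence level or the stated proportion.

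**Step 3. Ask what sample size would give ±18 points.**

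n = 1.96² × 0.16/0.18² = 19.0, so about 19 participants, not 70.

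**Step 4. Look for where 18% could have come from.**
- Full width of the interval for overall retention: 2 × 9.37 = 18.7 points (Wald), 18.5 (Wilson), 19.9 (exact).
- Half-width for a difference in retention between two arms of 35, both at 80%: 1.96 × √(0.16/35 + 0.16/35) = 0.1874, or 18.7 points.

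The two Wald results are algebraically identical, since 2 × √(0.16/70) = √(0.32/35). The number alone therefore cannot show which was calculated. Both are slightly above 18.

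**Step 5. Set the intervals against Table 1, if observed retention were 80%.**
- Stated margin: 80 ± 18 = 62% to 98%. This lies above the 60% Red line by 2 points.
- Wald: 70.6% to 89.4%. This lies above the Red line by 10.6 points.
- Wilson: 69.2% to 87.7%. This lies above the Red line by 9.2 points.

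All three straddle the 80% Green/Amber boundary.

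**Step 6. Allow for Table 1's survivor denominator.** The article gives no expected mortality, so the number of survivors is an assumption:
- all 70 survive: ±9.4 points
- 63 survive (10% deaths): 1.96 × √(0.16/63) = ±9.9 points
- 56 survive (20% deaths): ±10.5 points

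The margin stays near 10 points across this range.

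**The case against.** The strongest reply is that nothing turns on the figure. The Quantitative analysis section treats feasibility outcomes descriptively and compares them with the progression criteria. Table 1 uses percentage cut-offs with no confidence-interval rule, so a 9- or 18-point margin leads to the same Go, Amend or Stop result. The error also runs in the cautious direction, because the trial is more precise than it says. All of this stands, and it limits the point to a reporting correction.

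A second reply is that 18% may be a legitimate figure for another quantity. The Secondary outcome measures section does plan to compare completion rates between the groups, and the between-arm margin is 18.7 points. That stands as a possible origin. It does not rescue the wording, because the sentence concerns calculating retention with a total of 70, and Table 1 has no between-arm criterion. A reader might equally infer that 18% is certainly the full interval width. That is the more natural explanation, but without a formula it remains an inference.

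A reader might also infer that ±18 points contradicts the claim of adequacy for the progression criteria. The figures do not support that. Even 62% to 98% excludes Red, and the correct interval does not settle Green against Amber either.

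Nor does the choice of 70 rest on this sentence alone. The section also cites case-mix data, a published source on feasibility sample sizes and timely completion.

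**Conclusion.** The stated margin is wrong as written. With 70 participants and 80% retention, the 95% margin of error for overall retention is about 9.4 percentage points (9.3 to 10.1 across the Wald, Wilson, exact and continuity-corrected methods), against a stated 18. This assumes that margin of error means the half-width and that retention is one proportion over all 70. The origin of the 18% is probably the full interval width but cannot be established from the article. The sentence misdescribes the figure under either candidate explanation.

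It would go too far to conclude that 70 is inadequate or that a progression decision is compromised: the error understates precision and no threshold uses it. It matters because it is the only numerical precision statement offered for the sample size, and readers will rely on it. Severity: minor reporting correction.

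**What to change.** Confirm what was calculated, then restate the sentence using one interval method throughout. Either of these would do:

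- *With 70 participants and 80% retention, the margin of error is about ±9 percentage points (95% CI about 71% to 89%, Wald).*
- *With 70 participants and 80% retention, the 95% CI is about 69% to 88% (Wilson), about 18–19 points wide.*

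The two should not be mixed. The Wilson interval is asymmetric about 80% (about 10.8 points below and 7.7 above), so it does not pair with a symmetric ±9.

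If retention will be calculated among survivors, as in Table 1, quote the margin for the expected number of survivors and state the mortality assumption (about ±9.9 points if 63 survive). If a between-arm difference was meant, say so and give 35 per arm as its basis.

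The cost is one sentence. The sample size, analysis and progression criteria do not change, and no more participants are needed.

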### Recruitment

This study will recruit patients from ICUs from three NHS Trusts: Oxford University Hospital Foundation Trust (OUHFT), Guy’s and St. Thomas’ NHS Foundation Trust (GSTT), and University Hospitals Coventry and Warwickshire NHS Trust (UHCWT). These trusts cover geographically diverse patient populations, including a range of case complexity, ethnic backgrounds, and levels of social deprivation.

### Intervention

The FACT self-management intervention is based on the common-sense model of self-regulation [23] and consists of four structured modules covering aspects of fatigue management, including (i) About fatigue; (ii) Managing your energy with the 5 Ps (Priorities, Pacing, Planning, Permission, Position); (iii) Strategies for everyday life; and (iv) Goal setting and making plans. The intervention is separated into 16 sections and includes information in the form of both videos and text, activities, as well as patient stories. It is available via a website with all information and activities available to download and accessible in multi-formats (infographics, videos, printable and editable documents). A printed booklet will also be available according to patient preferences.

Patients will be encouraged but not required to move through the topics in the order presented and will be able to use the intervention at their own pace, repeating any topics if desired. As described in “Trial Design”, participants will receive a 30-min supportive phone or video call with an HCP from the ICU follow-up team at three months post-discharge. During this call, the HCP will assist with goal setting and action planning. To ensure consistency and quality of delivery, HCPs will attend an online training session and follow a defined protocol. In addition, a manual for research delivery nurses has been developed, which includes a clear timeline and action checklist to guide screening, recruitment, and participant follow-up. To support the delivery of the intervention, supportive call materials have also been prepared, including a supportive phone call structure and example scripts to help HCPs conduct the phone calls effectively and maintain fidelity to the intervention framework.

The control arm will receive usual care across all the research sites; existing inpatient ICU follow-up services are offered. These include inpatient ICU follow-up services, and patients who were in ICU for more than 72 h are offered outpatient services three months after hospital discharge, where physical and psychological health outcomes are evaluated. Where necessary, appropriate referrals and treatment plans are made. In addition, patients may also have access to generic information about recovery after critical illness available on a variety of websites (ICU Steps, criticalcarerecovery.com), which includes information about fatigue.

This trial is funded for a period of 20 months and commences in October 2025. It is anticipated that recruitment will be completed by the end of 2025. Final assessments, data analysis, reporting and write-up of results/findings will be completed by May 2026.

### Data management

All study data will be entered into REDCap, a secure, validated electronic data capture system. REDCap ensures data accuracy and integrity through a range of built-in checks, automated error detection, and logging of data modifications. The system is programmed to only allow data entries within predefined value ranges, minimising the potential for errors. Participants will be identified within REDCap by a unique, trial-specific identification code. To ensure data quality, regular data audits will be conducted by the Trial Management Group to identify and correct inconsistencies. Staff responsible for data entry will undergo training to standardise procedures and minimise errors. These procedures adhere to Good Clinical Practice (GCP) standards and ensure the reliability of all data collected during the study.

No identifying personal information will be stored alongside the trial data to ensure participant confidentiality. Participants will be allocated a trial-specific identification code and will only be referred to by the code on all research documentation. For paper-based questionnaires returned to the Trial Management Group (TMG), the data will be manually entered into REDCap by research staff. During the study, all electronic data will be securely stored in REDCap. The Google Drive folder will be double password protected and accessible only to authorised members of the research team. Paper copies of questionnaires and informed consent forms will be stored in a locked filing cabinet in a secured office at Oxford Brookes University. Audio recordings of participant interviews will be downloaded immediately after recording and saved as MP3/MP4 files on the Oxford Brookes Google Drive along with the transcriptions of these interviews. Once transcripts have been checked for accuracy, the recordings will be deleted from the recording devices and Google Drive. At the end of the study, all research data will be archived on the Oxford Brookes approved long-term data repository, Arkivum. This data set will not be opened, and data will be stored for a period of 10 years, after which it will be automatically deleted.

### Outcome measures

The primary and secondary outcome measures for this study are designed to evaluate the feasibility, acceptability, retention, and preliminary effectiveness of an HCP-supported self-management intervention for fatigue after critical illness. The outcomes will inform the design and implementation of a future large-scale trial. Furthermore, fidelity and acceptability of the intervention are measured by assessing adherence, estimated frequency, and patterns of use.

#### Primary outcome measures

The primary outcome focuses on the willingness of people affected by fatigue after critical illness to participate in an RCT evaluating an HCP-supported, self-management intervention. Recruitment and retention rates are critical indicators.

Recruitment rate is defined as the number of participants recruited or randomised as a proportion of those eligible and approached. This rate will be assessed at baseline and calculated both overall and by the research site.

Retention rate is defined as the proportion of participants who complete all the required questionnaires and semi-structured interviews. This outcome is essential to evaluate participant engagement and the feasibility of collecting follow-up data.

Assessments will be completed via phone or video call at baseline, three months, and six months post-randomisation. During the baseline data collection phase, additional demographic information (including age, sex, ethnicity, employment status, and marital status) and medical history (including comorbidities, primary diagnosis on ICU admission, ICU length of stay, hospital length of stay, days of mechanical ventilation, and severity of illness assessed by the APACHE III [22] will also be collected.

The progression criteria for full trial are summarised in Table 1.

**Table 1 Tab1:** Progression criteria

Category	Recruitment	Retention and follow-up completion	Remedial action
Green (Go)	> 85% anticipated (> 60 participants)	At least 80% of survivors will provide complete follow-up data	Continue—no action needed. Apply for further funding
Amber (Amend)	50–85% anticipated (36–75 participants)	60–80% of survivors will provide complete follow-up data	Continue—action needed. Explore ways to improve recruitment/retention
Red (Stop)	< 50% anticipated (< 35 participants)	< 60% of survivors will complete follow-up data	Stop. Explore reasons for poor recruitment/retention

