#### Secondary outcome measures

The secondary outcomes aim to estimate retention and the variability of outcome measures and evaluate the acceptability and fidelity of the intervention.

To estimate retention and the variability of outcome measures to inform sample size calculations for a future effectiveness study, completion rates of outcome questionnaires at baseline, three months, and six months post-randomisation will be assessed. These questionnaires will provide comprehensive data on participants’ fatigue levels, coping strategies, functional impairment, symptom responses, and health-related quality of life. Additionally, a comparison between the intervention group and the control group in terms of completion rates and results of questionnaires will be conducted to investigate whether the intervention creates an impact that differentiates the two groups. The questionnaires include the following:

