### Data analysis

#### Quantitative

Assessments will be performed at baseline, three months, and six months post-randomisation to evaluate feasibility and acceptability. Descriptive statistics will be employed to summarise the baseline demographic and clinical characteristics of both groups. Categorical variables will be reported as frequencies, percentages, and 95% confidence intervals (CI). Continuous variables that are approximately normally distributed will be summarised as means with standard deviations (SD) and 95% CIs. Continuous variables that are non-normally distributed will be summarised using medians with interquartile ranges (IQR).

Feasibility outcomes (including recruitment and retention) will be analysed using descriptive statistics only, consistent with feasibility study methodology. These outcomes will be compared against the pre-specified progression criteria to determine whether they are practical and appropriate to proceed to a definitive RCT.

An analysis of data in the questionnaires will explore potential differences between the groups and whether there is a difference in the change between the groups before and after the intervention to assess the effectiveness of the intervention in reducing fatigue and improving overall quality of life.^1^ Analyses will be conducted based on intention-to-treat (ITT). As this is a small study, treatment effects are likely to have wide CIs and consequently inferences will be tentative and reported as such. Results will be reported in accordance with CONSORT extension to randomised pilot and feasibility trials [16]. A summary of outcome measures, data types, and analysis is listed in Table 3.

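### Retention is defined over participants, interviews included, in the outcome text, but over survivors with follow-up data in the progression criteria used to judge it

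*Protocol article*

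**What the plan says.** Retention appears in four places in the protocol article.

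- **Primary outcome measures, text.** "Retention rate is defined as the proportion of participants who complete all the required questionnaires and semi-structured interviews". The base is participants, and the interview is part of the numerator.
- **Primary outcome measures, Table 1.** Green is "At least 80% of survivors will provide complete follow-up data", Amber is "60–80% of survivors will provide complete follow-up data", and Red is "< 60% of survivors will complete follow-up data". The base is survivors in every row. Interviews are not mentioned, and what makes follow-up complete is not defined.
- **Sample size.** "Anticipating a participant retention rate of 80" per cent, in a section where "we have a target sample of 70 participants with 1:1 randomised to the intervention and control arms". The base is again participants.
- **Secondary outcome measures.** Retention is addressed once more through questionnaires alone: "completion rates of outcome questionnaires at baseline, three months, and six months post-randomisation will be assessed".

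The Data analysis section (Quantitative) links the outcome to the cut-offs. Speaking of recruitment and retention, it says: "These outcomes will be compared against the pre-specified progression criteria to determine whether they are practical and appropriate to proceed to a definitive RCT".

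**The concern.** A rate built on one definition is to be judged against thresholds written for another. A participant who dies before six months counts against retention if the base is participants, and drops out of the calculation if the base is survivors. A participant who returns every questionnaire but gives no interview is not retained under the outcome sentence, yet may count as complete under Table 1.

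Deaths during follow-up are plausible. Entry requires Level 3 care in the ICU, the only survival-related exclusion is an expected survival of 30 days or less, and follow-up runs to six months.

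Retention is one of the two quantities that decide whether to proceed, amend or stop. Fixing the criteria in advance serves little purpose if the analyst can still choose the denominator and numerator once the data are in.

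**Working it through.** **The plan's own retention figure.** The Sample size section gives a margin of error of about 18% for 80% retention with 70 participants at 95% confidence. The usual half-width is 1.96 × √(0.8 × 0.2 / 70) = 9.4 percentage points, and the full interval width is 18.7. The stated figure therefore resembles the full width and is not reproduced as a margin. Nothing below depends on it. It does show that the 80% was considered against a base of 70.

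**Inputs from the article.** 70 randomised; Green at 80% or more, Amber at 60–80%, Red below 60%. Exactly 80% falls in both the Green and the Amber row; I count it as Green.

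**Inputs assumed.** The number of deaths *d*, varied from 4 to 14 (about 5–20% of 70), and the number of questionnaire completers. The article gives neither.

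**One example.** With *d* = 7 there are 70 − 7 = 63 survivors. Suppose 51 provide all follow-up questionnaires.

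- Over survivors: 51/63 = 81.0%, Green.
- Over participants: 51/70 = 72.9%, Amber.

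**Range.** The smallest count that earns Green over survivors is 0.8 × (70 − *d*), rounded up. The last column divides that count by 70.

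| Deaths | Survivors | Smallest Green count | Over survivors | Over 70 |
|---|---|---|---|---|
| 4 | 66 | 53 | 80.3% | 75.7% (Amber) |
| 7 | 63 | 51 | 81.0% | 72.9% (Amber) |
| 10 | 60 | 48 | 80.0% | 68.6% (Amber) |
| 14 | 56 | 45 | 80.4% | 64.3% (Amber) |

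As few as 2 deaths are enough at the borderline: 55/68 = 80.9% (Green) against 55/70 = 78.6% (Amber).

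**How far the denominator alone can go.** A result at the Green line over survivors becomes Red over participants only if 0.8 × (1 − *m*) < 0.6, where *m* is the proportion who die. That requires *m* above 25%.

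**The interview.** Each questionnaire completer without an interview leaves the numerator under the outcome sentence, so the rate can only fall. The size of the fall cannot be worked out from the article, because it states neither how many participants are to be interviewed nor the expected uptake.

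**The case against.** The best defence is that Table 1 is the operative rule and is explicit: all three rows say survivors. The outcome sentence says participants, without adding that this means everyone randomised, so the specific rule may be read as refining the general one. Likewise, the word required in the outcome sentence could limit the interview to those selected for it, and complete follow-up in Table 1 could be meant to include the interview. These readings are possible, but the article states none of them. The Sample size section applies 80% to participants with 70 in view, which points the other way on the denominator. The two statements still have to be reconciled.

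Several further points in the plan's favour stand:

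- The Secondary outcome measures section already plans questionnaire completion at each visit, by group, to inform the future sample size. The attrition allowance for the full trial therefore does not rest on the disputed definition alone.
- Requiring the whole set of questionnaires is strict, but Table 1 also asks for completeness. That is not a difference between the two.
- Table 3 and Fig. 1 could not be read here. If either fixes the denominator, the outcome sentence and Table 1 would still disagree as worded.

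A reader might also infer that the interview requirement caps retention at a very low figure because only a subsample will be interviewed. The article does not support this. It describes interviews with participants without restriction, and its purposive sampling concerns the healthcare professionals.

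**Conclusion.** The point holds as a contradiction within the stated decision rule; it is not a matter of missing detail. The denominators differ outright, and the numerators differ on their face. Under the assumed deaths, a result at or just above the Green line over survivors is Amber over participants at every level examined from 4 to 14 deaths. The interview requirement can lower it further by an amount that the article does not allow one to state.

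A reader might go further and say that one data set could come out Green, Amber or Red. That takes a second assumption on top of the deaths. If, say, only 41 of the 51 completers in the example were also interviewed, the outcome sentence would give 41/70 = 58.6%, which is Red. The article supplies neither assumption, and the denominator alone reaches Red from the Green line only above 25% mortality. The supported conclusion is a shift from Green to Amber under plausible but assumed mortality, plus an unresolved question about whether interviews count.

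**What to change.** Use one definition of retention in the outcome sentence, Table 1 and the Sample size section. It should state the denominator, the instruments, the time points and whether interviews count. One suitable wording is the proportion of randomised participants alive at the follow-up time point who provide the required three- and six-month questionnaires. The interview should come out of the numerator, because it does not measure whether outcome data are available.

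Report separately:

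- the same numerator over all randomised participants;
- interview uptake among those invited;
- the per-visit questionnaire completion already planned under Secondary outcome measures.

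The cost is wording in three places, with no new data. The change should be made before the retention results are seen.
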